## Abstract

**Introduction:** Functional Neurological Symptom Disorders (FNSD) are associated with high levels of disability and immense direct and indirect health costs. An innovative interdisciplinary rehabilitation approach for individuals with functional neurological symptoms of motor type–Nocebo-Hypothesis Cognitive Behavioral Therapy (NH-CBT)—combines CBT and movement retraining with video feedback embedded in a comprehensive explanatory model of the etiology of FNSD.

**Methods:** This protocol describes the development and implementation of a phase II, parallel group, randomized controlled trial with blinded outcome assessors to compare the efficacy of NH-CBT with an active control condition (supportive counseling and movement retraining). Individuals meeting diagnostic criteria of an FNSD or psychogenic movement disorder will be randomly assigned to one of the 8-week interventions. Self-report scales of motor and other physical symptoms, symptom-related psychological variables, and assessor ratings of participants' mobility will be administered at baseline, and at 8- and 16-week follow-up. Adverse events will be monitored across all sessions and therapeutic alliance will be measured at the end of therapy. The primary statistical analysis will test the hypothesis that NH-CBT is more effective than the control intervention at the 8-week follow-up.

**Discussion:** The therapeutic strategies of NH-CBT are theory-driven by assumptions of the predictive coding model of the etiology of FNSD. Strengths and limitations of this trial will be discussed.

**Trial registration**: Australian New Zealand Clinical Trials Registry (ANZCTR; identifier: ACTRN12620000550909).

## Introduction

Symptoms of altered voluntary motor function that cannot be explained by a neurological disorder are core features of the motor type of Functional Neurological Symptom Disorder (FNSD) (1), or Conversion Disorder as an official term alongside FNSD, and psychogenic movement disorders (PMD) (2). Weakness or paralysis, abnormal movements (e.g., tremor), abnormal gait, and limb posturing are typical motor symptoms. The incidence of persistent functional motor symptoms is estimated to be 4–12/100,000 per year (3). People with functional motor symptoms usually experience severe distress and disability (4), comparable to those with progressive neurodegenerative conditions (5). They are at increased risk of developing comorbid mental health disorders (e.g., major depression, anxiety disorders) (6) and of utilizing health-care resources at high rates (7) resulting in increased direct costs to healthcare systems and indirect costs based on work disability (4).

These epidemiological characteristics highlight the urgent need for effective treatments. FNSD or PMD is one of the most common diagnoses of new referrals to neurological services (8), however over 50% of these individuals do not improve or even feel worse at follow-up (9). There is currently no Class I evidence supporting the efficacy of any treatment for functional motor symptoms (10). The most promising evidence seems to come from cognitive behavioral therapy (CBT) and physiotherapy (11, 12). The central goal of CBT is to identify and modify dysfunctional thinking patterns (e.g. ingrained core thoughts about oneself or one's body, somatic misinterpretations), linked to the motor symptoms, and to promote behavioral changes. For example, typical CBT strategies include psychoeducation (e.g., understanding mechanisms of symptoms), functional behavioral analysis of symptom triggers, taking control of movements, and training of assertive communication (13). In a pilot randomized controlled trial (RCT), participants who underwent CBT tailored for functional motor symptoms significantly improved in daily functioning and secondary outcomes (14). The central goal of physiotherapy is motor reprogramming (15). Usually a systematic strategy is adopted that involves re-establishing elementary movements in affected body regions and reinforcing normal movement, while ignoring abnormal movements. More complex motor tasks are added as soon as individuals are able to perform simple movements appropriately, incrementally approximating normal movement.

Similar to other syndromes of persistent physical symptoms (e.g., chronic pain), mechanisms underlying functional motor symptoms are assumed to be multidimensional and need multidisciplinary interventional approaches. Accordingly, the active ingredients of CBT and physical therapy should be combined into a multidisciplinary approach to optimize outcomes. A consensus recommendation by physiotherapists, neurologists and neuropsychiatrists who are extensively experienced in treating functional motor symptoms, proposed to embed physiotherapy in a biopsychosocial framework (16). This was a first attempt to move toward embedding physiotherapy in psychological (mainly CBT-based), interventions addressing dysfunctional illness beliefs, self-directed attention, psychoeducation, and self-management strategies (16). Non-controlled effectiveness trials of such multidisciplinary treatment programs have demonstrated that combining CBT-based and physiotherapy strategies could be a promising approach for individuals with functional motor symptoms. McCormack et al. (17) and Jacob et al. (18) showed that participants' motor symptoms, mobility, and daily functioning significantly improved. Jordbru et al. (19) combined in a 1-week treatment a physiotherapy intervention following the principles of motor reprogramming (15) and embedded it in psychoeducation and CBT strategies. However, the application of CBT in these studies has generally focused on reducing the stress caused by functional neurological symptoms, rather than altering the underlying beliefs that may be causing the symptoms. Moreover, whilst these previous interventions fit the definition of a multidisciplinary approach (17, 18) or an interdisciplinary approach (19), their strategies do not appear to be integrated around a comprehensive theoretical framework that clearly defines the mechanism behind functional symptoms.

The predictive coding model has become a valuable approach to explain functional motor symptoms (20, 21). This model describes body perceptions as the result of a continuous process of generating, testing, and refining hypotheses of our perceptual system. Learned knowledge about the world is conceptualized as a set of neural representations or “priors” in a hierarchical model. Incoming sensory inputs vary in how well they match with existing priors. The resulting “prediction error” depicts the proportion of input that is not predicted by the prior. Our perceptual system constantly tries to keep this prediction error as low as possible to maintain homeostasis (22). Based on previous experiences a prediction can be more or less “precise” or “strong,” depending on the variance of its distribution. Edwards et al. (20) hypothesizes that functional motor symptoms can emerge based on sensory input (e.g., from a precipitating event or random discharges of neuronal activity) that is afforded excessive precision and strength by attentional processes. The motor symptoms are maintained by the “overweighting of prior beliefs over sensory data.” In accordance with the theory, clinical observations often confirm that distraction can result in a normalization of symptoms. Consequently, the precision of strength of the abnormal prior should be reduced and it should no longer elicit movements when attention is diverted. To our knowledge, there has only one previous treatment been published, a specialist physiotherapy for functional motor symptoms, that is based on the predictive coding model. Nielsen et al. (23) showed moderate effects of this treatment on health-related quality of life in a feasibility RCT.

In contrast to Nielsen et al. (23), we developed an interdisciplinary intervention, Nocebo-Hypothesis Cognitive Behavioral Therapy (NH-CBT), that is unique regarding the way in which elements of psychological and physiotherapy are combined. All disciplines involved in NH-CBT organize their therapeutic input around the direct and transparent addressing of illness beliefs as the primary target for their therapeutic input. The nocebo-hypothesis (NH) part of NH-CBT is proposed to be a crucial concept for the psychoeducation. The concept of a nocebo effect can provide this essential conceptual link between a “prior” and the motor symptom, in a way that most people with FNSD can comprehend. Embedded in the predictive coding model, a nocebo effect is explained as “negative health-related changes in the mind-brain body unit” (24) that are initiated and modulated by expectations (or “priors”). The nocebo effect has originally been studied as a side effect reported in the placebo arm of pharmacotherapy trials (25). Over time the nocebo effect has been extended and has been used to describe adverse effects of stimuli that individuals believe are likely to have negative health effects, e.g., radiation emitted by cell phones (26). Negative expectations can be generated by external sources (e.g., explicit warnings of specific side effects that can occur from a treatment) or just by increased general awareness about the potential of a stimulus to cause health problems (e.g., the belief of an individual that they are especially sensitive to effects of a medication) (26). In people with functional motor symptoms, a subconscious belief that there is neurological damage affecting the function of parts of their body is assumed to be a pathological mechanism. NH-CBT embeds physical interventions in CBT strategies and has the singular aim of disproving the (explicit and/or implicit) belief that the person is neurologically damaged or diseased. In this sense, it follows the traditional CBT's concept of a behavioral experiment, with the “evidence” invariably provided by video feedback in this case.

Compared with previous treatments combining CBT strategies and elements of physiotherapy for functional motor symptoms, NH-CBT has four basic treatment principles that all build on assumptions of the predictive coding model of functional motor symptoms:

Participants have to understand the role of their “priors” or beliefs as the key mechanism behind their symptoms.It is essential to provide the participants with new and precise “motor input” to lower the precision and strength of their abnormal prior beliefs, to develop a new belief, and to help increase the precision and strength of this new belief.The precision of the new motor input can be further increased and the abnormal prior belief should be modified by promptly providing participants with visible feedback about their movements.Participants' attention has to be diverted to lower its precision-increasing effect on abnormal priors.

Richardson et al. (27) previously examined the effects of NH-CBT in a retrospective case series design without a control group. The authors examined the effect of the treatment protocol in 12 patients with either weakness/reduced mobility, or tremor, or non-epileptic seizures, or mixed symptoms. In seven of the 12 episodes a clinically reliable and significant change of the functional motor symptoms was reached.

The central aim of this RCT is to investigate if NH-CBT for participants with persistent functional motor symptoms is more effective in improving physical functioning (primary outcome) (hypothesis 1) and secondary outcomes (hypothesis 2) in comparison to an active control intervention at the end of therapy. We will also examine if treatment effects can be maintained over 8 weeks post-intervention (hypothesis 3). Participant characteristics at baseline will be investigated as moderator variables of the intervention effect on an exploratory basis.

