The first part of the *psychological assessment* is a clinical interview where the principal investigator (MR) will provide individuals interested in participating with more detailed information about the study. We will explain to potential participants that we will offer them one of two treatments: one is conventional and more commonly used for individuals with FNSD, and has been found to be effective; and the other is new, and we are yet to establish evidence of its efficacy. Participants will be blinded to details of the content and proposed mechanisms of NH-CBT and the control treatment, and to differences between both treatments. They will only be informed that the core component of both treatments will be movement retraining, delivered by a rehabilitation professional. During the first part of the psychological assessment we will assess whether individuals meet all eligibility criteria and will ask them to give written consent to participate. In the second part, an assessor who is independent of this study and trained in applying the assessment tools will do the *baseline assessment*. The research assistant will do the Simplified Functional Movement Disorder Rating Scale (S-FMDRS) (30), the Functional Mobility Scale (FMS) (31) and the 10 m-Walk Test (32) with the participant. A physiotherapist will be present to ensure the safety of the participant. Participants will complete a baseline questionnaire including questions about demographic variables and all other outcome measures (see *Outcomes and Assessments*).

Participants will then be randomly assigned to receive either NH-CBT or the active control treatment over the following 8 weeks. At the end of the intervention period (*8-week follow-up*) participants will attend another assessment with an independent, blinded assessor and will complete all outcome measures. Sixteen weeks after baseline, participants from both groups will complete all outcome measures again (*16-week follow-up*). At that point, participants in the control group who have not achieved symptom remission will be offered NH-CBT and will be asked to complete a final questionnaire after 8 weeks of treatment (*24-week follow-up*).

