#### Sample Size, Power Calculations, and Interim Analyses

The power analysis for our trial was run with G^*^Power 3.1.9.4. In a previous trial, a physiotherapy for functional motor symptoms reached a moderate effect (*f* = 0.33) at 6-month follow-up on the SF-36 Physical Functioning subscale, our primary outcome (23). For this trial we conservatively assume a small group^*^time interaction effect (*f* = 0.10) under consideration of our three measurements and a test-retest reliability of *r* = 0.5. A power analysis for a mixed-effect ANOVA with an alpha error probability of 0.05 and a power of 0.80 results in an optimal total sample size of 164. A dropout rate of 5% is estimated based on our clinical experience and a recently completed trial that evaluated physiotherapy for individuals with FNSD (23). Accordingly a sample size of 172 participants is planned to be recruited.

We will, however, allow eight interim analyses every 22nd patient, conducted by a person who is independent of the day-to-day activities of the trial. Using the Lan-DeMets alpha spending function (55) we have gained appropriate boundaries or *p*-values for each interim analysis that would indicate a necessary stop and would allow an early conclusion of the trial (see Table 3). We used R 4.0.2 (56) and the ldbounds package (57) to gain Lan-DeMets boundaries. This approach helps to control for alpha-error accumulation with repeated interim analyses.

**Table 3 T3:** *P*-values (based on Lan-DeMets alpha spending function) indicating a necessary stop of the trial and needed sample size at each interim analysis.

**Interim analysis**	**Sample size**	***P*-value**
1	22	0.00000003
2	44	0.00009
3	66	0.001
4	88	0.005
5	110	0.013
6	133	0.024
7	155	0.036
8	172	0.050

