#### Statistical Analysis

Analyses will be based on intention-to-treat principles and will be carried out at the end of the last follow-up assessment. We will apply a linear mixed-effect model with baseline adjustment with main effects (fixed effect) for time (level 1, contrasts to baseline at 8- and 16-week follow-up) and group (level 2), group-by-time cross-level interaction term (8- and 16-week follow-up), and a generalized covariance matrix to account for dependency among observations. In order to deal with missing values, maximum likelihood estimation will be applied. Patterns of missing values will be assumed to be random. The outcomes of interest will be the group-by-time interaction at week 8 (hypothesis 1 and 2), and at week 16 (hypothesis 3). Effect sizes (Cohen's d) with 95% CI of changes between baseline and 8- and 16-week follow-up, as well as of between-group differences at 8- and 16-week follow-up will be investigated. Further sensitivity analyses will be conducted depending on the dropout rates and pattern of dropout reasons. For this purpose the linear mixed-effect models described above will be rerun for defined subgroups of the total sample (e.g., for participants with complete datasets only). To test for moderation (exploratory research question) we will add the moderator variable to the linear mixed-effect model described above (level 1: time; level 2: group) and will analyze a 3-level interaction. A significance level of 5% will apply to all analyses. Statistical analyses will be conducted with SPSS.

A limitation of group analyses is that it provides no information about the relative proportions of participants who did or did not respond to a treatment, which is based on a set standard. In accordance with recommendations by the Initiative on Methods, Measurement, and Pain Assessment in Clinical Trials (58), we will compare the distribution of participants with an improvement of at least 30 or 50%, no change, or deterioration on the primary outcome between the study groups with χ^2^-tests. Groups will be compared regarding adverse therapy effects, measured with the Inventory for the Assessment of Negative Effects of Psychotherapy, with independent sample *t*-tests and χ^2^-tests. To assess interrater reliability of the treatment fidelity ratings, intraclass coefficients (two-way random model with measure of agreement) for each item will be computed.

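### Hypothesis 3 is worded as maintenance of the effect from week 8 to week 16, but its assigned test shows only whether an arm difference is present at week 16

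*Protocol article*

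**What the plan says.** The Introduction gives the third aim as "We will also examine if treatment effects can be maintained over 8 weeks post-intervention (hypothesis 3". Study Design and Procedure fixes the starting point of that period: "At the end of the intervention period (*8-week follow-up*) participants will attend another assessment with an independent, blinded assessor". Maintenance over the following 8 weeks is therefore a question about week 8 to week 16.

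Statistical Analysis describes a baseline-adjusted linear mixed model whose time effects are "contrasts to baseline at 8- and 16-week follow-up". It then allocates model terms to hypotheses: "The outcomes of interest will be the group-by-time interaction at week 8 (hypothesis 1 and 2), and at week 16 (hypothesis 3". It also plans Cohen's d with 95% confidence intervals for "changes between baseline and 8- and 16-week follow-up, as well as of between-group differences at 8- and 16-week follow-up will be investigated". The only decision criterion given is "A significance level of 5% will apply to all analyses". The article names no contrast between week 8 and week 16, no retention margin and no minimum share of the effect to be kept.

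**The concern.** The hypothesis and its assigned test address different quantities. Write d8 and d16 for the between-arm differences in change from baseline at weeks 8 and 16. Maintenance is a statement about d16 − d8, or about d16 as a share of d8. The week-16 interaction tests d16 = 0. A significant result shows that some benefit is present at week 16. It does not show how much of the week-8 benefit was kept. A non-significant result does not show that the benefit was lost.

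The article names the test for this hypothesis, so the mismatch lies in what it fixes and not in a detail left to an analysis plan that is not shown. Durability also matters to this trial's own case. The Discussion presents the controlled follow-up as an important strength and says the trial should inform how well the effect is sustained. Control participants not in remission are offered NH-CBT at week 16, so weeks 8 to 16 are the only controlled evidence on durability.

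**Working it through.** **Inputs from the protocol article.** Planning effect f = 0.10 for the group-by-time interaction, three measurements, r = 0.5, and "alpha error probability of 0.05 and a power of 0.80 results in an optimal total sample size of 164" (Sample Size, Power Calculations, and Interim Analyses). Allocation is 1:1 (Methods for Minimizing Bias).

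**Assumptions, not in the article.** Outcome SD of 1 at each visit, compound symmetry, two-sided 5% tests, full evaluable N = 164.

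**1. The plan's own figure.** For the repeated-measures interaction, λ = f²·N·m/(1 − r) = 0.01 × 164 × 3/0.5 = 9.84, with df1 = 2 and df2 = (164 − 2) × 2 = 324. Power is 0.805 at N = 164 and 0.7998 at N = 162. The smallest even N is 164, so the figure reproduces.

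**2. Planning effect as a standardized difference.** If the arms differ by (0, d, d) at the three visits, then f = d/√18, so d = 0.1 × √18 = 0.424. If they differ by (0, d, d/2), then d = 0.1 × √24 = 0.490.

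**3. Week-16 significance threshold.** Baseline adjustment could mean change scores or conditioning on baseline, so both are shown.

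| Form | Variance | SE = √(4 × variance/164) | 1.96 × SE |
|---|---|---|---|
| Change score | 2(1 − 0.5) = 1 | 0.156 | 0.306 |
| Conditional on baseline | 1 − 0.5² = 0.75 | 0.135 | 0.265 |

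An observed d8 of 2 × 0.265 = 0.53 or 2 × 0.306 = 0.61 could thus halve and remain significant. That is 0.53/0.424 = 1.25 to 0.61/0.424 = 1.44 times the planning effect.

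**4. Chance of a significant week-16 result when exactly half the true effect is lost.** This is Φ((d/2)/SE − 1.96). For d = 0.424 and change scores: Φ(0.212/0.156 − 1.96) = 0.27.

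| True d8 | Change score | Conditional on baseline |
|---|---|---|
| 0.424 | 27% | 35% |
| 0.490 | 35% | 44% |
| 0.66 | 56% | 68% |

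The 0.66 is 2 × 0.33, an assumed reading of the effect that the article cites from an earlier physiotherapy trial.

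**5. Chance of missing a fully maintained planning effect.** 1 − Φ(0.424/0.156 − 1.96) = 0.225 for change scores, and 0.12 conditional on baseline.

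**6. The direct contrast.** Var(d16 − d8) = Var(d16) + Var(d8) − 2·Cov. Per unit of 4/N, this is 1 + 1 − 2 × 0.5 = 1 for change scores, and 0.75 + 0.75 − 2 × 0.25 = 1 conditional on baseline. The SE is 0.156 either way, and the 95% half-width is 0.306 SD, or 0.306/0.424 = 72% of the planning effect. The covariance term cannot be read from two separate intervals. Ignoring it in the change-score case would give √2 × 0.156 = 0.221, a half-width of 0.43.

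**7. What the direct contrast can show.** Power to detect loss of half the effect is 27% at d = 0.424 and 56% at d = 0.66. A one-sided 2.5% test that more than half is retained (d16 − 0.5·d8 > 0, SE = √(4 × 0.75/164) = 0.135) has power of 35% and 68% respectively when the effect is fully retained.

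**The case against.** Four points on the other side have weight.

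- **The planned effect sizes.** A reader might infer that the durability conclusion would rest on two p-values. The article does not support that: d with its interval is planned at both visits, so a large fall would be visible. What is missing is an estimate and interval for the fall itself.
- **No stated decision rule.** A reader might also infer that p < 0.05 at week 16 would be declared maintenance. No section says so. The Introduction speaks of examining the question, and the Discussion describes a controlled assessment at the end of treatment and 8 weeks later. Both are compatible with asking whether the benefit is still present at week 16. If that is what is meant, the test is right and the wording of the hypothesis should change.
- **The size of the problem.** It is tempting to say that half the effect could typically be lost unnoticed. At the planning effect the opposite holds: a halved effect would usually not be significant. Halving becomes compatible with significance more often than not only at effects of about 0.66 SD, and the Discussion expects a small group difference. The 12 to 23% miss rate is also ordinary type II error.
- **Scope.** The extra contrast is a linear combination of terms already in the model, which a full analysis plan might contain. That would excuse silence. It does not remove the mismatch, because the article explicitly assigns a different term to hypothesis 3.

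Finally, the specified test is the between-arm difference in change from baseline. It should not be read as a within-group comparison with baseline.

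**Conclusion.** The point holds as a minor mismatch between a secondary hypothesis and its test. The week-16 interaction answers whether NH-CBT is better than control at week 16. It does not answer whether the week-8 advantage was maintained, and no planned output gives an interval for that change.

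The halving example illustrates what the test cannot distinguish. It does not predict what this trial will find. All the calculated sizes rest on equal SDs, compound symmetry, r = 0.5 and the full evaluable sample; the article supplies only f, r, N and the number of measurements. The mismatch itself does not depend on those assumptions. The primary endpoint at week 8 and the sample size stand.

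**What to change.** Either of two changes resolves it:

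1. Keep hypothesis 3 as maintenance. From the same mixed model, pre-specify the group-by-time contrast at week 16 minus week 8 with its 95% confidence interval. Interpret hypothesis 3 from that estimate together with the week-16 difference, and state that a non-significant change will not be read as proof of maintenance. If maintenance is to be formally concluded, a retention margin has to be set in advance.
2. Reword hypothesis 3 as superiority of NH-CBT over control at week 16. The existing test then fits.

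Neither change needs new visits, data or participants; the first adds one contrast to a model already planned. Its cost is in interpretation: with a half-width of about 0.31 SD, it gives an honest estimate but rarely a decisive answer, and wording on durability will often have to be cautious.
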